## 2. Trial purpose

This study is to evaluate the efficacy and safety of hemoporphin for injection for the treatment of port-wine stains using placebo as the control in two stages of PDT treatments. Primary endpoint will be established at the first stage, and safety analysis will include both stages.

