- 5) Precautions: the patients should be instructed to observe the photoreaction after drug infusion and pay attention to photo protection. The photoreaction is expected to disappear completely in approximately 10 days after drug infusion. During the light protection period (2 weeks), the subjects should pay attention to protection of the exposed skin and eyes, avoid irradiation of sunlight or strong indoor lights. In case of drug extravasation during the infusion, the extravasation area must be kept completely away from light for a fairly long time until local swelling and discoloration disappears completely, otherwise severe local skin photoinjury may occur.
- 6) PDT may cause the following treatment reactions: the patients may experience itching, burning sensation, pain, swelling, blisters and scabs at the irradiated and surrounding area. These therapeutic responses are usually transient and self-healing without special treatment.
- 7) Adverse reactions: If light protection measures are not taken properly, some patients may experience photosensitive reactions such as photosensitive dermatitis, photosensitive ophthalmia, photosensitive cheilitis, etc; some patients may experience nausea, dizziness, headache, drowsiness, total bilirubin elevation, hyperpigmentation, hypopigmentation,

treatment site infection, scarring and other adverse reactions.

- 8) At week 8 after the first treatment, if the color of treatment area has not subsided completely and there are no serious pigmentation, scarring and other conditions that are unsuitable for re-treatment according to the investigator's judgment, the next stage treatment can be carried out.

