## 14.2 Statistical Analysis Method

### 14.2.1 Demographic Characteristics

(1) Consistency with normal distribution: Because this is a randomized and blinded trial with a large sample size, the data is acceptable when close to normal distribution. Appropriate statistical methods or data transformation will be adopted for non-normal distributed data, D method, W method or moment method will be used.

(2) Presence of outliers: statistical and clinical analysis should be carried out to determine the acceptance and rejection.

(3) Handling of the missing values of primary efficacy index: if the primary efficacy data of an individual subjects is missing, missing data were imputed as non-responses.

(4) Analysis of the subjects who did not complete this trial: the cause of each dropout case should be analyzed.

(5) Descriptive statistics: provide the mean, standard deviation, maximum, minimum, median, confidence interval, frequency (constituent ratio), etc.

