### 14.2.2 Statistical inference method

(1) Measurement data: t-test, paired t-test, rank sum test, paired rank sum test, median test method, etc.

(2) Numeration data: chi-square test, Fisher's exact test, etc.; Redit analysis and CMH method can be used to test the ranked data.

(3) Primary efficacy: The response rate will be analyzed using Cochran–Mantel–Haenszel test. Logistic regression analysis, with center and PWS type as covariates will be used to compare treatment group versus placebo group on primary efficacy. If baseline variables are not balanced between groups, non-balanced variable will be also included as covariates in the model. For response rate at week 8, missing data were imputed as non-responses.

(4) Difference analysis: in primary efficacy analysis, a 40% difference between the treatment and placebo group in response rate is expected to be detected.

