### 14.2.3 Statistical presentation

- (1) The report mainly uses the self-evident tables that include title, notes and number of cases.
- (2) The results of repetitively measured data use both tables and the annexed statistical charts at the same time to improve readability.
- (3) Difference analysis is represented by the two-sided 95% confidence interval for the intergroup difference in efficacy; all the general statistical tests are two-sided tests,  $P \leq 0.05$  is considered to have statistical significance.

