#### 14.5 Contents of statistical analysis

1. Case distribution: provide the sizes of different data sets of all groups, distribution of the cases among all centers, comparison of the total dropout rate, and a detailed listing of the reasons for termination.
2. Comparability analysis: demographic data and other baseline indexes are compared to measure the intergroup comparability.
3. Compliance analysis: (1) Drug compliance analysis: compare whether the patients of the two groups have taken the correct doses of trial drugs in timely manner without using the prohibited drugs and food as described in this protocol. (2) Drug combination analysis: count the number of subjects receiving drug combination in each group and provide a detailed list.
4. Efficacy analysis: PP and ITT analysis of the primary efficacy should be carried out at the same time; because this study is a multicenter clinical trial, the impact of center effect on the efficacy should be considered during analysis.
5. Analysis of the efficacy influencing factors: if there are significant differences in age, gender, disease types, disease conditions and other factors between the two groups before drug treatment or relevant factors significantly affecting the efficacy (e.g. drug combination) during the trial process, these factors should be used as covariates for analysis of covariance or logistic regression analysis during intergroup efficacy comparison.
6. Safety analysis: based on the requirements for correlation of adverse reactions, use listings to describe the AEs and adverse reactions in both groups (including the number of cases of various

AEs, the number of cases with "normal shift to abnormal" or "exacerbation of the abnormality" of the laboratory test indexes and abnormal conversion rate before and after this trial), list the causes and explain. Chi-square test is used for statistical analysis of the adverse reactions.

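### For adverse reactions the protocol names a chi-square test and no between-group interval; adding risk differences with 95% intervals and a small-count rule would be a cheap improvement

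*Protocol*

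**What the plan says.** Protocol section 2 makes safety an objective alongside efficacy: "This study is to evaluate the efficacy and safety of hemoporphin for injection for the treatment of port-wine stains using placebo as the control". Section 4.3 item 7 names reactions that may occur, ending with "treatment site infection, scarring and other adverse reactions", but gives no rate for any of them.

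Section 14.5 item 6 sets out the safety analysis. It is to "use listings to describe the AEs and adverse reactions in both groups", with case counts, laboratory shifts and an abnormal conversion rate. The one inferential sentence is "Chi-square test is used for statistical analysis of the adverse reactions".

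Section 14.2.3 item 3 gives the general rules. On estimation: "Difference analysis is represented by the two-sided 95% confidence interval for the intergroup difference in efficacy". On testing: "all the general statistical tests are two-sided tests", with P at or below 0.05 as the threshold.

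Two general lists also bear on the point. Section 14.2.2 names "chi-square test, Fisher's exact test, etc" for count data, without saying when each applies and without mentioning safety. Section 14.2.1 says to "provide the mean, standard deviation, maximum, minimum, median, confidence interval, frequency (constituent ratio), etc", under a heading on demographic characteristics.

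Section 3.1 sets 330 v 110 subjects. That figure comes from a regulatory minimum of 300 in the trial group plus an allowance for dropout. The control group receives placebo in the first course only.

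**The concern.** For efficacy the protocol asks for a test and an interval for the group difference. For harms it names only a test. Listings and counts show what happened, but not how large a difference the data leave open.

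This matters most for infrequent reactions. With one placebo subject for every three on the drug, expected placebo counts are small, and the uncorrected chi-square behaves differently in the two directions. A sizeable excess under hemoporphin can miss the threshold, while a couple of chance events under placebo can cross it. A reader given only the P value could take the first result as no difference and the second as an advantage for the drug. Neither reading would be sound.

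**Working it through.** **Inputs.** From the protocol: 330 and 110 subjects (3.1); chi-square for adverse reactions (14.5 item 6); two-sided tests with threshold P≤0.05 (14.2.3). Assumed: every event rate below, and that reactions are tested one by one with the uncorrected Pearson statistic.

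**The plan's own figure.** The only sample-size figure concerns efficacy: 75% v 35%, two-sided α=0.05, power 90%, 3:1, giving 66 and 22. It is reproduced. The unpooled formula with continuity correction gives 66.8 and 22.25, and exact Fisher power at 66 v 22 is 0.903. No power or detectable difference is stated for safety, so there is no safety figure to reproduce.

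**Two sparse tables (no event rate needed).** With x events under hemoporphin and y under placebo, χ² = 440·[x(110−y) − y(330−x)]² / [330·110·(x+y)·(440−x−y)].

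- 11 v 0: 440·1210² / (36,300·11·429) = 3.76, P=0.052 (Fisher 0.073). Expected placebo count 11·110/440 = 2.75.
- 12 v 0: χ²=4.11, P=0.043 (Fisher 0.043). With no placebo events, this is the first significant result.
- 0 v 2: 440·660² / (36,300·2·438) = 6.03, P=0.014. Fisher: (110/440)·(109/439) = 0.062. Expected placebo count 0.5.

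**Behaviour with no true difference.** If both rates are 1%, exact enumeration of two binomials gives rejection with placebo worse in about 3.5% of trials and with hemoporphin worse in about 0.005%. The total is below 5%, but nearly all of it favours the drug.

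**Power to detect a harm (exact enumeration, 330 v 110).**

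| Assumed rates, hemoporphin v placebo | Power | Missed |
|---|---|---|
| 3% v 0% | 29% | 71% |
| 4% v 0% | 67% | 33% |
| 5% v 0% | 90% | 10% |
| 3% v 1% | 10% | 90% |
| 5% v 1% | 46% | 54% |
| 5% v 2% | 21% | 79% |
| 10% v 5% | 35% | 65% |
| 20% v 10% | 70% | 30% |
| 15% v 5% | 86% | 14% |

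With 10% fewer subjects (297 v 99), power falls to 7% for 3% v 1%, 18% for 5% v 2%, 31% for 10% v 5% and 81% for 5% v 0%.

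**What an interval adds.** The Newcombe interval combines the Wilson limits (l, u) of each group. The lower limit is d − √[(p₁−l₁)² + (u₂−p₂)²] and the upper limit is d + √[(u₁−p₁)² + (p₂−l₂)²].

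- 11/330 v 0/110: Wilson limits 1.87% to 5.87% and 0% to 3.37%; d=3.33. Lower: 3.33 − √(1.46² + 3.37²) = −0.3. Upper: 3.33 + 2.54 = 5.9 points.
- 10/330 v 1/110: P=0.22; difference 2.1 points (−2.2 to 4.7).
- 33/330 v 6/110: P=0.15; difference 4.5 points (−2.0 to 9.3).

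None of the three is significant, yet each leaves an excess of more than 4 points open.

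**The case against.** The strongest reply is that the protocol never makes the chi-square a safety decision rule. The test follows listings, case counts and laboratory shifts, so 11 scars against none would be visible whatever the P value. This stands. A reader might infer that a non-significant result is meant to count as evidence of safety, but no section says so.

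Second, section 14 leaves detail to a statistical analysis plan that is not at hand, and that plan may add safety intervals. This also stands, and it limits the weight of the point. Mentioning efficacy in 14.2.3 does not forbid intervals elsewhere, and 14.2.1 lists confidence intervals among descriptive statistics. What remains is that the protocol does choose a method for harms, and it is the less informative one.

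Third, 14.2.2 lists Fisher's exact test, the usual choice for both sparse tables above, and under it the 0 v 2 result is no longer significant. This is fair, but the list is not tied to safety, and the sentence on adverse reactions names chi-square alone.

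Fourth, the power figures depend on the rates chosen. This is true: across plausible rates the share of harms missed runs from about 10% to nearly 100% (96% for 2% v 0%), so no single range should be quoted as a property of the trial. If the test is meant for overall incidence, counts would be larger and the sparse-table problem smaller.

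Finally, sizing a trial for efficacy and a regulatory minimum is not an error.

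**Conclusion.** The point holds as a cheap improvement, not as a flaw that undermines the trial. The protocol fixes a P-value method for harms and words the between-group interval for efficacy only, although safety against placebo is an objective.

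The asymmetry between 11 v 0 (P=0.052) and 0 v 2 (P=0.014) follows from the group sizes and the uncorrected statistic, with no assumed rate. The low power, such as 21% for 5% v 2%, does rest on assumed rates, on the full 330 v 110 and on testing reaction by reaction. The documents support saying that a non-significant P could be misread as no difference. They do not support saying that the protocol adopts that reading or rules out safety intervals.

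**What to change.** In section 14.5 item 6, replace the chi-square sentence with wording to this effect: for each adverse reaction and each laboratory shift in the placebo-controlled first course, the risk difference between groups is reported with a two-sided 95% score-type interval (Newcombe or Miettinen-Nurminen); any P value comes from Fisher's exact test where an expected count is below 5; and a P value above 0.05 is not read as absence of a difference. In section 14.2.3 item 3, extend the interval from efficacy to efficacy and adverse reactions.

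The safety conclusion should not be tied to the upper limit, since no margin is set. The intervals are there to show what the data leave open.

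The cost is wording and a few more table columns, with no extra subjects or data. There are three limits. Many intervals will be wide, so the safety statement becomes more modest. Fisher's test adds no power; with no placebo events it also first reaches significance at 12. And at very small counts the interval and Fisher's test can disagree. For 0 v 2 the Wilson limits are 0% to 1.15% and 0.50% to 6.39%, so the Newcombe upper limit is −1.82 + √(1.15² + 1.32²) = −0.07 points, which just excludes zero, while Fisher gives 0.062. Such results should be shown with their counts and not read against a threshold.

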## 15. Ethics

### 15.1 Ethics committee

The trial protocol and ICF must be approved by the “Medical Ethics Committee of Peking University First Hospital”; the approval notice issued by the ethics committee must be obtained before initiating this trial.

### 15.2 GCP guideline

Implementation of this trial complies with the national GCP guidance to protect the subject's rights, safety and interests effectively and ensure the reliability of clinical trial data.

### 15.3 Subject's ICF

The investigators must explain all the ICF contents approved by the ethics committee to the subjects before initiating this trial and obtain the written informed consent signed and dated by the subjects or their legal representatives; a copy of the ICF must be made available to the subjects after obtaining the informed consent.

If both the subjects and their legal representatives are illiterate, a witness should be present throughout the informed process. After a detailed explanation of the ICF, the subjects or their legal representatives can give verbal consent and the witnesses should sign and date the consent form. When it is impossible to obtain the subject's consent in advance in case of specialty (e.g. emergency), it is necessary to obtain consent from the legal representatives and inform the subjects or their legal representatives of the relevant trial situation as early as possible; the trial can proceed if they give their consent.

## 16. Data storage

For purpose of evaluation and supervision by the SFDA and sponsor, the investigators should save all the study data including all the patient's ICF and CRFs, detailed drug dispensing records and other materials with confirmation by the participating subjects (for effective verification of different recorded data such as CRF and hospital's original records) and the original signatures. The investigators should maintain the above data for 5 years after the ending of this clinical trial.

The ownership of all data of this clinical trial belongs to the sponsor Shanghai Fudan-Zhangjiang Bio-Pharmaceutical Co., Ltd.; unless required by the SFDA, the investigators should not disclose

these data to any third party by any means without written approval of the sponsor. Approval by the sponsor in advance is required when the investigators publish the study results in scientific journals or present them at academic conferences. The sponsor has the rights to use these reports for academic promotion purposes.
